#### Patient-reported outcomes and cortisol biomarker

i. Patient-reported outcomes

Participants will complete several patient-reported outcome measures to evaluate fatigue—Brief Fatigue Inventory (BFI),^
68
^ sleep quality—Pittsburgh Sleep Quality Index (PSQI)^
76
^ and depression—Centre for Epidemiologic Studies Depression (CES-D)^77,78^ at Week-1, Week-6, Week-12, and Week-16.

a. Fatigue—The Brief Fatigue Inventory (BFI)

The BFI was developed for the rapid assessment of fatigue severity in cancer patients for use in both clinical screening and clinical trials. It is easy to administer, and patients can complete them easily as it has only 9 items with simple wordings that are easy to understand and translate.^
68
^ Items 1 to 3 rate participants’ worst, usual, and current fatigue during the past 24 hours using a visual analog scale (VAS) ranging from 0 (no fatigue) to 10 (very severely fatigued). A composite fatigue severity score was obtained by averaging the 3 severity scores. The remaining 6 items rate the level at which patients` fatigue interferes with certain functions such as daily activity, work, walking ability, normal work, relations with others, and enjoyment in life. Each item is rated on a scale of 0 (does not interfere) to 10 (completely interferes). A composite fatigue interference score will be obtained by averaging the scores of the 6 interference items. Severity scores of 1 to 3 suggest mild fatigue, 4 to 6 moderate, and 7 to 10 represent severe fatigue. The internal consistency Cronbach’s α at .96 supports the reliability of BFI which is correlated with measures of performance status (patients who are more ill reported higher levels of fatigue).^
68
^

b. Sleep—Pittsburgh Sleep Quality Index (PSQI)

The PSQI, proposed by Buysse et al^
76
^ in 1989, is currently the most commonly used scale for assessing sleep quality. The PSQI is a 19-item scale measuring 7 aspects of the sleep quality and disturbances, that is, subjective sleep quality, sleep latency, duration, efficiency, disturbances, use of sleep medication, and daytime sleep dysfunction, each weighted equally on a 0 to 3 scale. The total score ranges between 0 and 21, with increasing scores indicating worse sleep quality.^
76
^ It has a sensitivity of 89.6% and a specificity of 86.5% to detect insomnia cases and is a useful first-line, easy-to-handle, and time-efficient questionnaire to evaluate sleep quality.^
79
^ The PSQI was reported to be a stable measure of sleep quality with high test-retest reliability and construct validity.^79,80^

c. Depression—Centre for Epidemiologic Studies Depression (CES-D)

The CES-D is a short self-reported 20-item scale^
81
^ to be administered to measure depression symptoms at baseline, mid-intervention, post-intervention, and follow-up. The CES-D shows very high internal consistency and adequate test-retest repeatability.^
81
^ The score is the sum of all items, and the maximum score is 60. Scores ≥ 16 on the CES-D is considered as having “depressed symptoms.” The cut off score of 12 has been validated with DSM-III criteria for clinical depression.^81,82^

ii. Cortisol biomarker: 24-hour urine cortisol

Urine sample will be collected at baseline (Week-1) and post-intervention (Week- 12).^
83
^ Participants are briefed on the urine collection procedure during assessment and advised to obtain the 2.5 L urine collection container from any nearby BP Laboratories before baseline (Week-1) and post-intervention (Week-12). We use 24-hour urinary cortisol as a non-invasive, integrated measure of cortisol stress hormone activity that could be collected in participants’ home environments. Participants are instructed to collect all urine for 24 hours from 8:00am a day prior to baseline (Week-1) and post-intervention (Week-12) to 8:00am the next mornings and to send the urine sample collected to the nearest BP Laboratories the next morning itself. If the 2.5L collection container is completely full, subjects are advised to use a clean mineral water bottle to collect any specimen in excess of the 2.5 L collection. If subjects are unable to collect all urine for any reason, their samples will be deemed inadequate and no urinary cortisol data will be recorded for these subjects.

The 24-hour urine cortisol test provides a more accurate estimate of overall cortisol secretion^
84
^ to assess urinary-free cortisol (UFC) over a 24-hour period and provides an index of (unbound serum cortisol) the total amount of cortisol released by the adrenals. The 24-hour collection time reflects the amount of cortisol that is released over a complete circadian cycle, which is a physiologically meaningful unit of time. An integrated mean of cortisol levels over a 24-hour period is thought to provide a moderately stable measure of adrenocortical output.^
85
^ Urinary cortisol output will be analyzed by chemiluminescent microparticle immunoassay (CMIA) at BP Laboratories, headquartered in Shah Alam, Selangor Darul Ehsan, Malaysia.

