### Study Assessments

The variables under consideration will encompass basic demographic data, primary outcomes, and secondary outcomes. Basic characteristics will be collected at baseline (Week-1).

Primary feasibility outcomes on adherence, attendance, and any adverse events will be recorded throughout the intervention period from Week-1 to Week-12 in the practice diary by the participants. Secondary patient-reported outcomes on fatigue, depression, and sleep will be measured at baseline (Week-1), mid-intervention (Week-6), post-intervention (Week-12), and 4 weeks after completion of intervention (Week-16). Urine samples (for urine cortisol test) to assess 24-hour urinary cortisol will be collected a day prior to enrollment date and post-intervention (Week-12). Primary feasibility outcomes and secondary patient-reported outcomes will be assessed by an independent research assistant to minimize bias. A summary of the planned data collection is shown in Figure 2.

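### The 24-hour urine rule acts only on known incompleteness and discards the data without a repeat; with no objective check described, the cortisol totals are unverified

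*Protocol article*

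**What the plan says.** The cortisol part of the Protocol article's section on patient-reported outcomes and the cortisol biomarker sets out the procedure in some detail.

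- **Setting.** The measure is chosen partly as one "that could be collected in participants’ home environments", so collection is not observed.
- **Window.** "Participants are instructed to collect all urine for 24 hours from 8:00am a day prior to baseline (Week-1) and post-intervention (Week-12"), ending at 8:00am the next morning.
- **Preparation and overflow.** "Participants are briefed on the urine collection procedure during assessment", and if the container is full "subjects are advised to use a clean mineral water bottle to collect any specimen in excess of the 2.5 L collection".
- **Acceptance rule.** "If subjects are unable to collect all urine for any reason, their samples will be deemed inadequate and no urinary cortisol data will be recorded". The text does not say who judges this or on what evidence, and it describes no second attempt.
- **Laboratory.** "Urinary cortisol output will be analyzed by chemiluminescent microparticle immunoassay (CMIA) at BP Laboratories". No completeness marker, volume limit or other plausibility check is named.
- **Interpretation.** The result is read as an index of "the total amount of cortisol released by the adrenals" over a full circadian cycle.

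Three other sections bear on this. Quantitative Data analyses by intention to treat with LOCF and also names a mixed model in which cortisol is an outcome. Feasibility Outcomes counts the nature and extent of missing data. Basic Demographic Data lists sex, marital status, age and cancer history, but not body weight.

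**The concern.** A 24-hour total scales with the fraction of urine that reaches the laboratory. The stated rule removes a sample only when a shortfall is known. With unobserved collection and only the cortisol assay named, an unreported loss passes, and so does a collection that ran too long. A participant whose shortfall is known loses the data point; one whose equal shortfall is unknown stays in. The rule therefore sorts samples by what is disclosed or noticed, which is not the same as completeness.

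Each participant has only two collections, so a single poor one goes straight into the change from Week-1 to Week-12. Cortisol is the one effect outcome that the abstract calls objective, and the Limitations section regrets reliance on self-report for the others. At stake are the precision of the cortisol comparison and an avoidable loss of data, some of which LOCF would turn into recorded zero change.

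**Working it through.** The plan gives no figure for collection error or rejection, so there is none to reproduce. The inputs below are assumptions with ranges, except where a source is named.

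**1. Size of a single undetected error.** If voids are equal, one missed void out of 8, 6 or 4 lowers the total by 1/8 = 13%, 1/6 = 17% or 1/4 = 25%. If excretion is even, an error of 1, 2 or 4 hours shifts it by 1/24 = 4%, 2/24 = 8% or 4/24 = 17%. A collection error e of 10% to 30% per visit is used below as the illustrative range.

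**2. Noise in the change score.** Assume true cortisol with mean scaled to 1, CV 50% (variance 0.25) and within-person correlation 0.6. Let the recovered fraction have mean 1 and SD e, independent of cortisol, of the other visit and of group.

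- Variance of true change: 2 × 0.25 × (1 − 0.6) = 0.20.
- Added by collection error: 2 × e² × (1 + 0.25) = 2.5e².
- Variance ratio: (0.20 + 2.5e²)/0.20.
- Reference effect: 0.20, the small effect size in the Sample Size section, which that section does not tie to cortisol.

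| e | added variance | ratio | 0.20/√ratio |
|---|---|---|---|
| 10% | 0.025 | 1.125 | 0.19 |
| 20% | 0.100 | 1.50 | 0.16 |
| 30% | 0.225 | 2.125 | 0.14 |

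**3. Cross-check at a single visit.** The factor on a standardised effect is CV/√((1 + CV²)(1 + e²) − 1). For e = 10%, 20%, 30% it is 0.98, 0.91, 0.83 at CV 50%, and 0.94, 0.82, 0.69 at CV 30%. The range 0.69 to 0.98 applied to 0.20 gives about 0.14 to 0.20, in line with step 2.

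**4. Rejected Week-12 samples under LOCF.** If the sample is treated as missing and baseline is carried forward, its change is zero. With a fraction q rejected, unrelated to the true change, mean change is multiplied by (1 − q): 0.9, 0.8 or 0.7 for q = 10%, 20% or 30%. With equal q in both arms, the difference between arms shrinks by the same factor. A rejected baseline has no earlier value to carry forward.

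**5. Complete pairs lost for want of a repeat.** The Sample Size section plans 60 participants with about 20% drop-out, so 60 × 0.8 = 48 remain. With rejection rate f per collection, complete pairs are 48(1 − f)²: 38.9 at 10% and 30.7 at 20%. If one repeat failed independently at the same rate, f would become f², giving 48 × 0.99² = 47.0 and 48 × 0.96² = 44.2. Participants who fail persistently would reduce that gain. This counts observed pairs; it is not the number entering a LOCF analysis.

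**The case against.** The strongest reply is that this is a condensed article. Creatinine, volume records, pooling of the overflow bottle, handling of the first void and a repeat window often sit in a laboratory manual or instruction sheet, and their absence here does not show that they are absent from the trial. What the text does state (a 24-hour window, a briefing, an overflow bottle, rejection of incomplete samples) is sensible. Cortisol is one of several secondary outcomes, the primary outcome is feasibility, and failed collections are part of what a feasibility trial should record.

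Much of this stands. Pooling and the first void are instruction-sheet detail and are not pressed. What remains rests on text the article does state: a rule triggered by known incompleteness, outright discard, and LOCF.

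A reader might infer three stronger things.

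- **That participants may collect about 32 hours by including both 8:00am voids.** The instruction says 24 hours, which excludes this.
- **That the baseline collection may come before its briefing,** because urine "will be collected a day prior to enrollment date and post-intervention (Week-12"). But the briefing sentence goes on to advise fetching the container before baseline, and Recruitment describes an earlier contact with a separate enrolment date.
- **That the sole test is the participant's own declaration.** That is an inference. The text does not say how incompleteness is established, and a laboratory might notice an obviously low volume.

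**Conclusion.** The point holds as a limited weakness in a secondary outcome. As described, completeness is unverified, known failures are discarded without a second attempt, and LOCF would record a rejected Week-12 sample as no change. On the assumptions shown, undetected error of 10% to 30% per visit takes a standardised effect of 0.20 to about 0.19 to 0.14, and 10% to 30% rejection at Week-12 shrinks the mean change by 10% to 30%. The CV, correlation, error and rejection rates are all assumed.

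A reader might go further and say that the cortisol measure cannot be trusted, or that a positive result could be an artefact of collection. The documents do not support that. Error unrelated to group attenuates; it does not create a systematic difference between arms. Because participants know their allocation, care in collecting at Week-12 could differ by arm, but nothing in the text shows that it would. The primary feasibility conclusion is not undermined, although avoidable rejections do add to its missing-data component.

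**What to change.** 1. Measure creatinine and record total volume on the specimens already sent to the laboratory. Two per participant gives at most about 120.
2. Before any results are seen, set completeness limits by sex and body weight. Add weight to the baseline form, since it is not among the listed characteristics.
3. Report cortisol with and without samples outside the limits.
4. Replace outright discard with one permitted repeat collection: before the first class for baseline, and within a fixed window at Week-12. Keep counting first-attempt failures as feasibility data.
5. State that baseline is not carried forward for a rejected Week-12 sample. Leave the value missing in the mixed model that the plan already names.

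If a laboratory manual already contains items 1, 2 or 4, citing it is enough for those items.

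The cost is a low-cost assay, one added baseline measurement, a few repeat collections and a short amendment to the analysis text. The downside is that some apparently complete samples will be flagged.

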#### Qualitative interview

Semi-structured interviews will be conducted to inform interpretation of quantitative results and participants’ acceptance, experience, and subjective perception of the study as well as to find out areas for further improvement^
86
^ after Week-16.

A prepared interview guide (Supplemental Material 4) is designed to delve into participants’ experiences and will be used in the interview to cover 3 primary themes: the experiences of practicing GQ, changes in the physical and emotional state, and suitability of GQ for cancer survivors. Examples of questions to be asked are “How do you feel about the 12 weeks of Guolin Qigong study?,” “Have you had other benefits from this Guolin Qigong study?,” and “Would you recommend Guolin Qigong to other cancer survivors? Why? Why not?.”

Each interview will take approximately 45 minutes and will be audio-recorded and transcribed verbatim by the Researcher.

## Protocol Amendments

The Researcher is responsible for submitting materials to the human ethics committee.

### Trial Monitoring

The Researcher will report progress of the trial to the panel of supervisors on a quarterly basis. Annual reports will be submitted to the human ethics committee to monitor the trial progress and outcomes. Participants in the GQ group will be advised to record any perceived adverse events in the practice diary and this will be recorded in participants’ Adverse Event Form by the Researcher. The severity, expectedness and causal relationship with GQ intervention will be assessed for every adverse event according to guidelines for safety reporting.^75,87^

The schedule of the enrollment, intervention, and data collection is shown in Figure 2.

### Sample Size

Using a small effect size (0.2)^
65
^ rather than a medium effect size (0.5)^
64
^ to achieve a more conservative estimation, the sample size is 25 cases in each group with 90% power and two-sided 5% significance trial design.^
88
^ Allowing for a drop-out of about 20% based on previous studies,^89
[Bibr bibr90-15347354241252698][Bibr bibr91-15347354241252698]-92^ a total sample of 60 (30 in each group) would be required.

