**Methods::**

This is an open-label randomized controlled trial with 60 participants divided into 2 study groups in a 1:1 ratio. The intervention group will receive 12 weeks of Guolin Qigong intervention with a 4-week follow-up while control will receive usual care under waitlist. The primary outcome will be feasibility measured based on recruitment and retention rates, class attendance, home practice adherence, nature, and quantum of missing data as well as safety. The secondary subjective outcomes of fatigue, sleep quality and depression will be measured at Week-1 (baseline), Week-6 (mid-intervention), Week-12 (post-intervention), and Week-16 (4 weeks post-intervention) while an objective 24-hour urine cortisol will be measured at Week-1 (baseline) and Week-12 (post-intervention). We will conduct a semi-structured interview individually with participants within 3 months after Week-16 (4 weeks post-intervention) to obtain a more comprehensive view of practice adherence.

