## Methods

### Study Design

#### Intervention/clinical trial

The primary objective of this study is to explore the feasibility of a GQ intervention in patients with various cancer types who experience CRF. This study includes the 3 most prevalent cancer types that is, breast, lung and colon cancers. This is a randomized-controlled trial that compares the GQ intervention group to a usual care waitlist control group receiving standard medical care allocated in a 1:1 ratio to evaluate the feasibility and effects of a 12-week GQ intervention on 60 eligible breast, lung, and colorectal cancer survivors’ fatigue, sleep quality, depression, and 24-hour urine cortisol change. Refer to Figure 1 for an overview of the study. This study protocol was developed based on the SPIRIT 2013 Statement (Standard Protocol Items: Recommendations for Interventional Trials) (Supplemental Material 1).^
66
^

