## Data Analysis

### Quantitative Data

Data analysis will be conducted by an independent statistician. Data analysis will be by intention to treat using last observation carried forward (LOCF).^
93
^ The normality of the study data will be checked by examining the mean, median, skewness, and kurtosis including graphical representation of the box plot, normal Q-Q Plot or histogram. Continuous data will be summarized using descriptive statistics including the number of observations used in the calculation (*n*), mean, standard deviation (SD), minimum, median and maximum. Categorical data will be summarized as counts and percentages of each category. Between group comparison will be conducted using the t test, chi-square test, or Fisher exact test, as appropriate. We will report the results for two-sided 5% tests for the primary trial outcome. We will use generalized linear mixed model (GLMM). The outcomes of the model will be BFI, PSQI, CES-D scores, and 24-hour urine cortisol test results. Models will include the treatment group as a fixed effect, with time as a random effect to account for the repeated measurements. Analyses will be conducted to identify the baseline characteristics of the participants who may benefit most from the intervention. Model assumptions will be checked and appropriate adjustments to the analysis will be made where necessary. STATA^®^ software version 17.1 (2021; Stata Corporation, College Station, TX, USA) will be used for all analyses. Cohen’s D will be calculated as the absolute differences between the mean change in the variable divided by pooled variance of the change.

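### The 90% power stated for 25 per group at effect size 0.2 is wrong as written: a single unadjusted comparison has about 11%

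*Protocol article*

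**What the plan says.** The Sample Size section opens "Using a small effect size (0.2"), a choice made "rather than a medium effect size (0.5") so that the estimate would be conservative. It continues that "the sample size is 25 cases in each group with 90% power and two-sided 5% significance trial design". No outcome, standard deviation or raw difference is attached to the effect size. The next step reads "Allowing for a drop-out of about 20% based on previous studies", and concludes that "a total sample of 60 (30 in each group) would be required".

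Elsewhere the purpose is feasibility. Under Study Design, "The primary objective of this study is to explore the feasibility of a GQ intervention", and the abstract likewise makes feasibility the primary outcome and fatigue, sleep quality and depression secondary. The hypotheses at the end of the Background give the feasibility criteria: about 80% to 85% retention and 75% to 85% class attendance. They also predict benefit on fatigue, sleep, depression and cortisol. The Quantitative Data section plans between-group tests and a mixed model for those four measures, and adds: "We will report the results for two-sided 5% tests for the primary trial outcome".

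**The concern.** The section ties four quantities together: effect size 0.2, 25 per group, 90% power, two-sided 5%. Fixing any three determines the fourth, and the stated combination is far from any that holds for two groups. Moving from 0.5 to 0.2 is called conservative, but a smaller effect should raise the required number several-fold, and 25 per group is too few even for 0.5.

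What is at stake is how the secondary results are read. Someone who trusts the sentence would take a non-significant fatigue, sleep, depression or cortisol comparison as good evidence against even a small effect. The data will be too imprecise for that.

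The same paragraph also sizes the trial on a power figure, whereas its primary question is whether feasibility rates meet stated thresholds. Precision, not power at 0.2, is what matters there.

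**Working it through.** **Inputs.** From Sample Size: d = 0.2 (alternative 0.5), n = 25 per group, power 90%, two-sided 5%, drop-out about 20%, 30 per group recruited. From the abstract: "60 participants divided into 2 study groups in a 1:1 ratio". The labels small 0.2 and medium 0.5 are the usual ones for Cohen's d, which the Quantitative Data section also names. Correlations are not given, so those used below are assumptions.

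**1. Trying to reproduce 25 per group.** Normal approximation: n = 2(1.960 + 1.282)²/d².
- d = 0.2: 2 × 10.507/0.04 = 525.4, so 526 per group; the exact t calculation gives 526.3, so 527.
- d = 0.5: 2 × 10.507/0.25 = 84.1, so 85 per group; the exact t gives 85.03, so 86.

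Neither gives 25. Other readings at d = 0.2 also fail (normal approximation): 429 per group one-sided, 393 at 80% power, 263 for a one-sample test. Baseline adjustment with one follow-up multiplies n by (1 − ρ²); reaching 25 needs ρ = √(1 − 25/526) = 0.976.

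The nearest variant reads 0.2 as Cohen's f for a group-by-time interaction. With four visits and ρ = 0.5 it needs 46 in total, and 28 to 94 over two to four visits and ρ of 0.3 to 0.7. That is near 50, but it depends on an unstated correlation and on a different meaning of 0.2.

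**2. Power actually available.** Two-sample t test, non-centrality d√(n/2), 2n − 2 degrees of freedom.

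| n per group | d = 0.2 | d = 0.5 |
|---|---|---|
| 24 | 10.4% | 39.6% |
| 25 | 10.7% | 41.0% |
| 30 | 11.9% | 47.8% |

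Setting power to 90% at n = 25 and solving for d gives 0.936.

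**3. Allowance for repeated measures.** Averaging three follow-ups with baseline adjustment, and a common correlation ρ, multiplies the variance by f = (1 + 2ρ)/3 − ρ². The effective difference is 0.2/√f.
- ρ = 0.5: f = 0.417, effective d = 0.310, power 18.9%.
- ρ = 0.7: f = 0.310, effective d = 0.359, power 23.8%.
- ρ = 0.8: f = 0.227, effective d = 0.420, power 30.7%.

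This gain is not available for cortisol, which has a single follow-up at Week-12.

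**4. Pilot-size reading.** Suppose the 90% and the 0.2 belong to a later main trial whose SD is estimated from a pilot of p per arm. Combined size is 2p + 2 × 2t²/0.2², where t is the 90th percentile of a non-central t with 2p − 2 degrees of freedom and non-centrality 1.960. The minimum is 1158.3, at p = 28; at p = 25 it is 1158.9, almost the same.

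**5. Drop-out.** 25/(1 − 0.20) = 31.25, so 32 per group. The stated 30 equals 25 × 1.2. After 20% loss, 30 × 0.80 = 24. Retaining 25 of 30 allows 1 − 25/30 = 16.7% loss.

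**6. Precision of the planned size.**
- Retention of 80%, exact (Clopper-Pearson) 95% CI: 48/60 gives 67.7% to 89.2%; 24/30 gives 61.4% to 92.3%.
- Standardised between-group difference at 25 per group, unadjusted: half-width 2.011 × √(2/25) = 0.569 SD.

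**The case against.** The best defence is that 25 per arm was never meant as an efficacy sample size. The trial is a feasibility study, the sizing sentence refers to a trial design and cites a source not available here, and step 4 shows that 25 per arm is close to optimal as a pilot for a 90%-powered main trial at 0.2. If so, the number is sound and only the description of the power is at fault. That is plausible and is a good reason to leave 60 alone. It remains an inference: the section mentions no later trial and presents the 90% as belonging to this sample.

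Four stronger readings are tempting, and the document does not support them.
- A reader might infer that the efficacy tests were sized for a conclusion they cannot deliver. The section names no endpoint, and feasibility is primary.
- A reader might take 11% as the power of the whole design. It describes one unadjusted time point; a repeated-measures model is planned and could do better, though still far below 90%.
- A reader might say that no between-group test can address the primary outcome. Retention and missing data exist in both arms and can be compared. Only class attendance and Guolin Qigong home practice are confined to one arm.
- A reader might conclude that a significant result should be barred or that the tests are invalid. Low power leaves the 5% error rate intact; it makes null results uninformative and estimates imprecise.

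The drop-out slip is also small. The text says about 20%, and going from 25 to 24 per group moves power only from 10.7% to 10.4%.

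**Conclusion.** The power statement is wrong as written and should be corrected; confidence in this is high. The shortfall against the claimed 90% is large on every reading of 0.2 as a standardised mean difference. The 11% rests only on the article's own figures and a standard two-group t test. The 19% to 31% rests on assumed correlations and on baseline adjustment that the article does not specify. On the pilot reading the error becomes one of attribution, but the sentence still needs changing.

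The sample size itself is not shown to be inadequate for the feasibility aim, and nothing here calls for 527 per group. The two-sided 5% test promised for the primary outcome is a related, lesser fault: it does not answer whether retention and attendance reach their thresholds. The drop-out arithmetic is a minor slip.

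**What to change.** Keep 60 participants and revise the text as follows.

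- **Sample Size, power.** Delete the claim of 90% power for this trial or, if it is what was meant, state that the 90% and the 0.2 refer to a later main trial. Present 60 as a feasibility size and give its precision, using the 48/60 retention interval and the half-width of about 0.57 SD from step 6.
- **Sample Size, drop-out.** State either that 30 per group leaves 24 after 20% loss, or that 25 completers allow for about 17% loss.
- **Quantitative Data, primary outcome.** Replace the promise of two-sided 5% tests with feasibility rates and exact 95% CIs, judged against the retention and attendance thresholds in the hypotheses.
- **Quantitative Data, secondary outcomes.** Report fatigue, sleep, depression and cortisol as between-group estimates with 95% CIs, and say that a non-significant result will not be read as evidence of no effect.

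The cost is wording only, with no added participants, visits or measurements. The stated power becomes less favourable.
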